## Abstract

**Introduction:**

Pain and disability after meniscectomy can be a substantial lifelong problem. There are few treatment options, especially for young people. Non-surgical management (rehabilitation) is an option but increasingly surgeons are performing meniscal allograft transplants (MATs) for these individuals. However, this is still an uncommon procedure, and availability and usage of MAT vary widely both in the UK and internationally. It is not known which treatment option is the most effective and cost-effective.

**Methods and analysis:**

The Meniscal Transplant surgery or Optimised Rehabilitation trial is an international, multicentre, randomised controlled trial. The aim is to compare the clinical and cost effectiveness of MAT versus an optimised package of individualised, progressive, rehabilitation that we have called personalised knee therapy (PKT).

Participants will be recruited from sites across the UK, Australia, Canada and Belgium. The planned 144 participants provide at least 90% power to detect a 10-point difference in the Knee injury and Osteoarthritis Outcome Score (KOOS4) at 24-months post randomisation (primary outcome). A prospectively planned economic evaluation will be conducted from a healthcare system and personal social services perspective. Secondary outcome data including health utility, occupational status, sports participation, mental well-being, further treatment, and adverse events will be collected at 3, 6, 12, 18, and 24 months. Analysis will be on an intention-to-treat basis and reported in-line with the Consolidated Standards of Reporting Trials statement.

**Ethics and dissemination:**

The trial was approved by the London—Bloomsbury Research Ethics Committee on 19 August 2022 (22/LO/0327) and Northern Sydney Local Health District Human Research Ethics Committee, NSW, Australia on the 13 March 2023 (2022/ETH01890).

Trial results will be disseminated via peer-reviewed publications, presentations at international conferences, in lay summaries and using social media as appropriate.

This protocol adheres to the recommended Standard Protocol Items: Recommendations for Interventional Trials (SPIRIT) checklist.

**Trial registration number:**

ISRCTN87336549.

STRENGTHS AND LIMITATIONS OF THIS STUDYInternational, multicentre, randomised controlled trial comparing an initial treatment strategy of meniscal allograft transplant (MAT) or personalised knee therapy (PKT) for adults with post-meniscectomy pain and functional loss.Participants will be recruited from sites across the UK, Australia, Canada and Belgium.Clinical outcomes assessed using the Knee Injury and Osteoarthritis Outcome Score in addition to a range of secondary outcomes.Rare clinical presentation that may result in difficulty recruiting.No radiological or biochemical measures to determine if MAT changes risk of osteoarthritis.

## Introduction

A meniscectomy is an arthroscopic procedure where part or all of the meniscus is removed following an irreparable tear. Meniscal tears are common, often as a result of sporting injuries in young people.^1^

Every year, approximately 80 000 people in England undergo meniscectomy.^2^ For the majority of people, pain and other symptoms, such as locking, improve after surgery. However, some people have ongoing problems with pain and functional loss, leading to many years of disability. Ten years after a meniscectomy, 20% of people have developed osteoarthritis, increasing to 50% after 20 years.^3 4^ An individual aged 30–39 years having a partial meniscectomy is 40 times more likely to need a knee replacement after 15 years than that of the general population.^5^

There are few treatment options for people suffering from post-meniscectomy problems. Knee replacement is not usually recommended until people are over 50 years old. Therefore, younger adults with post-meniscectomy pain often have to live with their symptoms until they are at an age when knee replacement may be considered appropriate.^6 7^ Increasingly, orthopaedic surgeons are performing meniscal allograft transplants (MATs) for people with post-meniscectomy pain.^8^ Availability, access and usage of MAT are, however, variable across the clinical community, resulting in a potential inequity in access to treatment. The transplant, which involves taking a donor meniscus from someone who has died and inserting it into someone with a similar-sized knee, is costly, at around £7500 per case in the UK, although costs will vary substantially worldwide.

Non-surgical management (optimised rehabilitation) is also a viable treatment option.^9^ The principles of care for early osteoarthritis could apply to this population, as rehabilitation has a strong evidence base in this (related) setting. Potential treatments include exercise, weight loss, lifestyle and activity advice, adjuncts such as orthoses and offloading braces, and non-steroidal anti-inflammatory drugs (NSAIDs); it is reasonable to think they could have a similar beneficial effect in the post-meniscectomy pain setting.^10–13^ If shown to be effective for persistent pain after meniscectomy, a package of optimised rehabilitation would be safer, and cheaper, and does not impact on an individual’s ability to work or undertake other activities compared with a postoperative phase.

There is a lack of high-quality evidence about whether MAT or non-surgical care is more effective and which is the most cost-effective treatment for post-meniscectomy pain and functional loss. Our 2019 systematic review included 19 studies (n=1731); 18 case series of MAT and just one randomised controlled trial (RCT) (this being a pilot study, n=21).^4^ Patient-reported outcomes improved from baseline across all studies. There are no data at present on non-surgical care for people with pain after meniscectomy; it would be very hard to make many meaningful comparisons of a programme unless baseline differences between groups were balanced through randomisation.

Currently, there are no comparative data (except our previous pilot study)^14^ to inform patients, clinicians or health commissioners about whether MAT should be used or whether patients with post-meniscectomy pain would be better treated with non-surgical interventions.^4^

## Aim

The aim of the study is to compare the clinical and cost-effectiveness of an initial treatment strategy of MAT or Personalised Knee Therapy (an optimised package of rehabilitation) for adults with post-meniscectomy pain and functional loss.

## Methods and analysis

### Trial design

The Meniscal Transplant surgery or Optimised Rehabilitation (MeTeOR2) trial is an international, multicentre, two-arm RCT comparing the clinical and cost- effectiveness of MAT with an optimised package of rehabilitation termed PKT. The planned trial start date was June 2022. The planned trial end date is November 2027.

This paper and the trial protocol were written following the Standard Protocol Items: Recommendations for Interventional Trials (SPIRIT) guidelines. Figure 1 shows the participant flow diagram, and a copy of the participant consent form is included in online supplemental file 1. A summary of core trial information is presented in the WHO trial registration data set in online supplemental file 2.

10.1136/bmjopen-2024-085125.supp1Supplementary data

10.1136/bmjopen-2024-085125.supp2Supplementary data

**Figure 1 F1:**
[figure not shown]
Meniscal Transplant surgery or Optimised Rehabilitation (MeTeOR2) participant flow diagram. IKDC, International Knee Documentation Committee; KOOS4, Knee injury and Osteoarthritis Outcome Score; EuroQol five-dimension questionnaire and Euroqol visual analogue scale (EQ-5D-5L).

### Patient and public involvement (PPI)

Patient involvement has been critical in the design and development of the trial and will continue to be important in its delivery, including the interpretation and dissemination of the results. As well as running several PPI events with patients who have experience of post-meniscectomy pain and either PKT or MAT, our research team includes two PPI representatives as coapplicants. Our PPI coapplicants are integral to the Trial Management Group (TMG) and are engaged in trial management meetings, contributing the patient perspective to trial processes and procedures and will be key to our dissemination plan. Two further people with post-meniscectomy pain sit on the Trial Steering Committee (TSC).

### Objectives

#### Primary objectives

To compare the clinical effectiveness of an initial treatment strategy of MAT compared with PKT, based on participant-reported knee function at 24-months post-randomisation, using the four-domain version of the Knee Injury and Osteoarthritis Outcome Score (KOOS4).To determine the cost effectiveness of MAT compared with PKT from a National Health Service (NHS) and Personal, Social Service (PSS) perspective.

#### Secondary objectives

To quantify and draw inferences on health utility, occupational status, sports participation, mental well-being, further treatment (including further surgery or physiotherapy in either arm) and adverse events (AEs) at 3, 6, 6, 12, 18 and 24-months.To evaluate process measures to compare days to initiation of treatment, rehabilitation attendance, and participant expectation of outcome.

### Outcome measures

Outcome measures were chosen in collaboration with our PPI representatives and our experienced clinical team. In line with SPIRIT guidance, details of the schedule of enrolment, interventions, and assessment can be found in online supplemental file 3.

10.1136/bmjopen-2024-085125.supp3Supplementary data

#### Primary outcome

The primary clinical effectiveness outcome is participant-reported knee function using the four-domain KOOS4 score 24-months after randomisation.^15^ This is a knee-specific instrument (0–100, 100 best score) incorporating four of the five domains of the full KOOS score (KOOS4 uses the domains for symptoms, pain, function/sports and quality of life, but not activities of daily living).^15^ The KOOS4 has been widely used in previous trials of knee surgery including those with young adult, non-arthritic populations and is well accepted by the clinical community.^14 16–19^

Cost effectiveness of the interventions will be assessed using health utility, occupational status, sports participation, mental well-being, further surgery (treatment switching or secondary knee surgery), satisfaction with the outcome of treatment, participant global impression of change and AEs.

#### Secondary outcomes

All collected at 6, 12, 18 and 24 months. As an additional pre-intervention baseline measure (to understand any changes occurring whilst participants wait for their intervetnion, given the potetnial discrepancy between groups), we will collect KOOS4, EQ-5D-5L, IKDC, Tegner and SWEMWBS scores in the four weeks leading up to the start of the participant's intervention.

The KOOS4 (also recorded at pre-intervention).The five individual KOOS domains (also recorded at baseline). A validated knee-specific instrument developed to assess the patients’ opinion about their knee and associated problems.Health utility using EQ-5D-5L (also collected at baseline, preintervention and 3 months).^20 21^
Short Warwick-Edinburgh Mental Wellbeing Scale (SWEMWBS, also collected at baseline and pre-intervention).^22 23^
Tegner activity/sport scale (also collected at baseline and pre-intervention).^24^
Satisfaction with the outcome of treatment using a 5-point Likert scale.^25^
The Participant Global Impression of Change. A single-item, 7-point Likert scale.^26^
The International Knee Documentation Committee (IKDC, also collected at baseline, pre-intervention and 24 months).^27^
Further knee surgery and physiotherapy.Resource use using participant questionnaires (also collected at 3 months).Analgesia use.

#### Safety outcomes

AEs and serious adverse events (SAEs) related to the surgery, anaesthetic, or rehabilitation will be collected according to relevant Warwick Clinical Trials Unit (WCTU) Standard Operating procedures (SOPs) at 3, 6, 12, 18 and 24 months post randomisation.

#### Process and fidelity measures

Days to initiation of randomised treatment, defined as the number of days between randomisation and the first physiotherapy contact for those who undergo PKT or the day of surgery.Physiotherapy attendance and intervention details will be recorded on physiotherapy case report forms (CRFs) at each appointment.A surgical CRF will be completed after each surgery including details about the anaesthetic and surgery such as surgical findings, surgical time, tourniquet time, graft size, fixation of graft, and additional procedures.

Alongside a detailed data management plan, the programming team at WCTU have built a bespoke database management system to store and maintain high-quality data for the duration of the trial.

### Eligibility criteria

#### Inclusion criteria

Pain and/or functional restriction from the knee, severe enough to warrant potential MAT in the judgement of the treating clinician.Previous meniscectomy ≥6 months ago.

#### Exclusion criteria

Symptomatic ligament instability, not previously corrected, as determined by the assessing clinicianCoronal limb alignment which requires surgical correction (previous correction, performed at least 6 months before entry to the trial, is not an exclusion criteria), as determined by the assessing clinician (Previous surgery (except prior MAT) will be allowed. Where people have mal-alignment or ligament deficiency (30% of the MAT population), alignment or ligament deficiency may be corrected by osteotomy or ligament reconstruction, which should have been performed at least 6 months before entering someone into the study).Age under 16 years, or if ≥16 years, open growth plate at the proximal tibia as judged by the clinical team on imaging taken as part of standard care.Full-thickness cartilage loss (exposed bone) >1 cm^2^ on routine clinical MRI, prior surgery, or any other form of clinical imaging or evaluation. This will be determined by the assessing clinician (it could be based on an assessment by a clinician or a radiologist, although the final decision rests with the treating clinician).Inflammatory arthritis affecting the study knee as determined by the assessing clinician (ie, a prior inflammatory event not considered to be related to the current clinical condition would not require exclusion).Unable or unwilling to engage with rehabilitation.Unable to adhere to trial processes.Previous randomisation in the present trial (ie, other knee). Where a previous randomisation has occurred in error, a participant may be withdrawn and this criterion will not apply.

### Participant identification, screening and withdrawals

Potential participants will be identified by clinical teams across the UK, Australia, Canada, and Belgium. Currently, sites in the UK and Australia are recruiting participants (UK ethical approval obtained 22 August 2022 and open to recruitment 7 March 2023, Australian ethical approval obtained 4 April 2023 and open to recruitment 8 December 2023). The centre in Canada has obtained ethical approval (20/11/2023) and plans to open to recruitment in Summer 2024. Ethical approval for sites in Belgium is pending but without a confirmed timeline yet.

Participant identification will typically happen in outpatient or intermediate care clinics, hospital waiting lists, patient discharge lists or referrals into hospital (from either primary, intermediate, or secondary care). Any potential participants will be assessed for eligibility by an appropriately delegated clinician. There is no requirement for any specific investigation although it is normal clinical practice to evaluate someone with a painful knee after prior meniscectomy with MRI scan for diagnostic purposes before any consideration of treatment options. This is likely to be the case for most participants but is not a requirement for entry. A screening log will be completed directly onto the trial database at all sites.

Those who are eligible will be given information about the trial and invited to discuss it further with a member of the local research team. They will be given adequate time to consider participation. Information sheets, invitation letters and other approved patient-facing materials may be posted, emailed, physically provided or shared via other means to potential participants. A member of the local research team will carry out the informed consent process, collecting either written consent or witnessed remote verbal consent, and baseline data collection.

### Randomisation

After consent and baseline data have been collected, participants will be randomly allocated to the two treatment groups via a central computer-based randomisation system provided by WCTU, independent of the study team. Randomisation will be a 1:1 allocation determined by a minimisation algorithm using age (≥30 years or <30 years), treating site and knee compartment (lateral or medial) as factors, with a random factor included to provide a 70% weighting towards balance across the trial.

Participants will be randomised sequentially at site level. Randomisation will be performed by any member of the local clinical or research team on the delegation log, using the online system. Depending on local site arrangements, stickers, electronic tags or an equivalent may be used on the participant’s clinical notes to flag their inclusion in the trial.

Randomised participants can choose to discontinue their treatment and/or withdraw from follow-up at any time, without prejudice. This will have no effect on their current or future care. All withdrawals will be monitored by the TMG and oversight committees.

### Trial treatments(s)/interventions

#### Group 1: MAT (surgical intervention)

Participants allocated to surgery will receive MAT once an allograft becomes available. Surgical procedures are outlined in a trial-specific surgical manual which was developed at a surgical consensus meeting (July 2022) and informed by the International Meniscus Reconstruction Experts Forum (IMReF) guidelines.^8^

Immunosuppression is not required as meniscal allografts have low cellular content and are not rejected in the way solid organ transplants might be. Donors are screened for blood-borne diseases according to approved tissue bank policies. Essentially, this is similar to blood donors and there are no reported cases of viral transmission from MAT.

It is possible that participants may have to wait for 6–12 months for a graft of the right size to become available (median 6.5 months in our pilot study).^14^ The delay to receive a graft is unavoidable in meniscal transplantation surgery, due to the availability of a suitable-sized donor graft from tissue banks. To reduce time to surgery, the dimensions of the graft needed will be sent to tissue banks according to surgeon preference and usual practice. Recovery following MAT plateaus after 9–12 months post surgery. As the primary outcome is at 24 months, recovery will still be completed by the primary outcome time point, even for people in whom surgery is delayed.

All care, including the choice of anaesthetic, the surgical procedure and post-operative analgesia, will be in accordance with usual procedures and care at participating sites.

Rehabilitation for the surgery group will be according to a standardised programme specific to MAT. We have used the lead centre’s established programme for this and, in discussion with participating centres, adapted it to ensure that it is deliverable across multiple NHS and international sites. A formal PKT programme will not be used prior to surgery in the MAT arm, although we do not discount people having prior or current physiotherapy.

#### Group 2: personalised knee therapy (non-surgical intervention)

The PKT programme is a tailored and optimised package of rehabilitation aimed at improving individualised outcomes for people with knee pain and/or functional limitation following meniscectomy. It was developed from a pilot study,^14^ and refined through literature and guideline reviews on non-surgical interventions including physiotherapy and other conservative interventions such as weight loss advice, knee braces and orthotics and referral to other services.^9–13 28–30^ This was supported with a consensus meeting held in July 2022, whereby experts in the field came together to develop a final comprehensive evidence-based PKT programme for the trial, ensuring that it is deliverable across all of our UK and international study sites. A template for intervention description and replication (TIDieR) checklist^31^ for describing interventions for the METEOR2 PKT intervention is included as online supplemental file 4.

10.1136/bmjopen-2024-085125.supp4Supplementary data

The PKT programme is outlined below:

##### Aim

To reduce pain, restore full knee range of motion, improve knee function and optimise overall social participation through a goal-setting approach personalised to the participant.

##### Delivered by

Physiotherapists trained in the principles of the METEOR2 PKT programme. Training includes the background to the problem of post-meniscectomy pain, the rationale for the trial, discussion about the PKT framework and trial administration procedures. Trained physiotherapists receive a comprehensive PKT manual containing a detailed account of all trial and intervention procedures.

##### Mode of delivery

As the intervention will be personalised to the participant, there is flexibility, as determined by clinical judgement and service provision, for PKT to be delivered face-to-face in acute hospital or community physiotherapy departments, through virtual consultation or a hybrid of the two.

##### Duration

Minimum of 3 months from the first assessment and a minimum of 4 sessions in total, but can be as many as clinically required, reflecting normal clinical practice.

##### Treatment starting point from randomisation

When an appointment with an appropriate physiotherapist is available, according to normal clinical waiting times.

##### Timing of consultations

The interval between consultations will be personalised to the needs of the participant based on their presentation, progress and treatment goals.

##### Assessment

Initial assessment will include participant’s history (subjective assessment) and physical examination (objective assessment). This will follow a routine musculoskeletal physiotherapy assessment. Specific focus in the objective assessment will be made on lower limb function and kinetic control, muscle length, strength, and recruitment. Shared goals will be discussed between physiotherapist and participant which will form the basis of the problem list and treatment plan.

##### Treatments

Based on the individualised problem list and goals developed by the physiotherapist and participant, the physiotherapist will deliver interventions aimed to specifically manage the presenting problems. Through this, a personalised approach is made to the participants rehabilitation, optimising their outcome. Each participant will be provided with a manual which will include their treatment goals, information about their PKT programme with details of specific individualised exercises, and an exercise planner to encourage adherence.

### End of trial

The trial will end when all 24-month follow-up data have been received and entered onto the trial database. The trial will only be stopped prior to this if mandated by the Research Ethics Committee (REC), following recommendation from the TSC, or if funding for the trial ceases.

The trial will be extended if we receive funding for 5, 10 or 15–20 year follow-up. Consent will be obtained for long-term follow-up.

## Safety reporting, AEs and SAEs

All AEs and SAEs will be defined using widely accepted standard criteria. For this trial, AEs and SAEs will be collected from the point of randomisation onwards, up to 24 months. To avoid unnecessary reporting, some events which occur during treatment and recovery will be considered as normal aspects of the therapy, anaesthetic and post-operative recovery processes unless in the opinion of the clinical team, they are untoward, excessive or outside of what might normally be expected for the procedure; these will not need reporting. We will only collect AEs and SAEs related to the participants’ knee, treatment they receive in the trial (or any treatment for the study knee), or trial processes.

SAEs will be reported to WCTU within 24 hours of the research staff becoming aware of the event. Events will be followed up until they are resolved, or until the end of the trial, and an outcome has been agreed.

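### The reporting exemption for normal treatment and recovery events uses an arm-dependent benchmark and is not expressly limited to non-serious events, so it could tilt the planned adverse event comparison toward MAT

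*Protocol article*

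**What the plan says.** Under Safety reporting, AEs and SAEs, the protocol article states that both kinds of event are collected from randomisation to 24 months. It then sets an exemption: "some events which occur during treatment and recovery will be considered as normal aspects of the therapy, anaesthetic and post-operative recovery processes". A judgement by treating staff can bring an event back into reporting; the wording of that exception is "unless in the opinion of the clinical team, they are untoward, excessive or outside of what might normally be expected for the procedure". For everything that stays within the exemption, the article says "these will not need reporting". A further restriction follows: "We will only collect AEs and SAEs related to the participants’ knee, treatment they receive in the trial". Events connected with other treatment of the study knee or with trial processes are also within scope. The next paragraph adds that "SAEs will be reported to WCTU within 24 hours of the research staff becoming aware of the event".

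Under Safety outcomes, the article says that "AEs and serious adverse events (SAEs) related to the surgery, anaesthetic, or rehabilitation will be collected" at 3, 6, 12, 18 and 24 months, following the trials unit's operating procedures.

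The use of these data is set under Secondary objectives: "To quantify and draw inferences on health utility, occupational status, sports participation, mental well-being, further treatment" and, at the end of the same list, adverse events. Under Primary outcome, adverse events also appear among the items by which cost-effectiveness will be assessed.

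**The concern.** A comparison of harms between arms needs events to be captured to the same standard in each arm. Three features of the exemption work against that.

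- **The benchmark depends on treatment.** Whether an event is waived turns on what is expected of the procedure. Swelling or stiffness can be ordinary after MAT and still reportable during PKT.
- **The headings lean toward surgery.** Two of the three exempt categories do not exist for a participant who never has an operation.
- **The filter is a judgement by treating staff.** The article does not describe blinding. With surgery compared against physiotherapy, randomisation done by local clinical or research staff, and notes that may be flagged, it is reasonable to infer that the clinical team knows which treatment was given.

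In addition, the exemption refers to events without qualification, directly after a sentence on both AEs and SAEs. A site is not told which sentence governs an event that is expected and also meets a seriousness criterion.

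At stake is a secondary objective on relative harm. The article's Introduction suggests that rehabilitation would be the safer option if effective, so the contrast is one that readers will look for. An event that was never recorded cannot be recovered by modelling or imputation.

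**Working it through.** The article gives no adverse event rates and no share of events expected to be waived, so it has no figure on this point to reproduce. The check sets the passages side by side and then shows how the filter would act under assumed values.

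**Step 1: which arm each exempt heading reaches.**

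| Exempt heading | MAT arm | PKT arm |
|---|---|---|
| Therapy | Yes: MAT has its own rehabilitation programme (Group 1 section) | Yes |
| Anaesthetic | Yes | Only after a switch to surgery |
| Post-operative recovery | Yes | Only after a switch to surgery |

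Treatment switching is anticipated (Statistical analysis plan section), so the PKT arm is not wholly outside the filter. By allocated arm, the weight still falls mainly on MAT.

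**Step 2: the exemption against the safety outcome.** Safety outcomes promises collection of events related to surgery, anaesthetic or rehabilitation. The exemption removes some events under almost the same three headings. The text does not say whether waived events are still recorded and merely not reported, or not captured at all.

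**Step 3: the exemption against the SAE rule.** Untoward, excessive or unexpected events stay reportable, and SAEs go to the trials unit within 24 hours. Neither sentence states that a serious but expected event falls outside the exemption, and neither states that it falls inside.

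**Step 4: direction and illustrative size.** Let pM and pP be the true proportions of participants with an event, and fM and fP the shares waived in MAT and PKT, counting one event per participant. Then

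- observed proportion = p × (1 − f)
- observed risk ratio = true risk ratio × (1 − fM)/(1 − fP)

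The factor (1 − fM)/(1 − fP) does not involve the event rates. It is below 1, favouring MAT, whenever fM exceeds fP. It equals 1 when they are equal and exceeds 1 when fP is larger.

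With 144 participants at 1:1, each arm has 144/2 = 72. Assume true proportions of 30% and 15%, which give 72 × 0.30 = 21.6 and 72 × 0.15 = 10.8 participants, a risk ratio of 2.0 and a difference of 15 points.

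| Waived MAT / PKT | Observed MAT | Observed PKT | Observed counts of 72 | Difference (points) | Risk ratio |
|---|---|---|---|---|---|
| 0% / 0% | 30% | 15% | 21.6 / 10.8 | 15 | 2.0 |
| 20% / 20% | 24% | 12% | 17.3 / 8.6 | 12 | 2.0 |
| 20% / 5% | 24% | 14.25% | 17.3 / 10.3 | 9.75 | 2.0 × 0.80/0.95 = 1.68 |
| 40% / 5% | 18% | 14.25% | 13.0 / 10.3 | 3.75 | 2.0 × 0.60/0.95 = 1.26 |
| 50% / 0% | 15% | 15% | 10.8 / 10.8 | 0 | 2.0 × 0.50/1.00 = 1.0 |

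If the true proportions were equal at 30%, waiving 40% and 5% would give 18% against 28.5%, a risk ratio of 0.63: an apparent safety advantage for MAT where none exists. The 50% / 0% row is an extreme, because the therapy heading makes zero waiving in PKT unlikely.

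**The case against.** A reader might infer that serious events will go unreported and so be hidden from the Data Monitoring Committee. The article does not say that. Untoward or excessive events remain reportable, and the 24-hour rule for SAEs is stated without exception. A prolonged hospital stay, for instance, is hard to call a normal aspect of recovery that is neither untoward nor excessive. What stands is narrower: no sentence limits the exemption to non-serious events.

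A reader might also infer that the economic evaluation is distorted. The Primary outcome section does list adverse events there. However, the Health economic evaluation section builds costs from resource-use questionnaires and QALYs from EQ-5D-5L, and neither is shown to depend on adverse event counts.

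Participant-reported KOOS domains, analgesia use, further surgery and physiotherapy, and resource use also capture part of the burden without passing through the clinical team's judgement. This softens the consequence, but it does not supply the adverse event comparison that the secondary objective calls for.

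The article condenses a full protocol, which may list the expected events, and collection follows the trials unit's operating procedures. The absence of a list here is therefore not the complaint. The stated rule is: even with a list, the exception rests on clinical opinion and on a procedure-specific yardstick.

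Finally, counting every ordinary post-operative symptom as an adverse event is not neutral either, since it loads expected recovery onto MAT. That is a fair point about where to draw the line, and the fix must allow for it.

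**Conclusion.** The concern holds as a risk of differential ascertainment, not as a demonstrated bias. As written, the exemption depends on clinical judgement against a benchmark that differs by arm, it leans toward events that only surgery produces, and it is not expressly limited to non-serious events. Since inference on adverse events is planned, it could bias that comparison toward MAT.

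The direction rests on one assumption: that a larger share of events is waived in MAT than in PKT. The headings make this plausible, but the article does not establish it. The size cannot be derived from the document. In the assumed scenarios with more waiving in MAT, a true risk ratio of 2.0 is observed as anything from 1.68 down to 1.0, and equal waiving leaves it unchanged. That the clinical team is unblinded is an inference from the design, not a statement in the article. The KOOS4 primary outcome is unaffected. A low-cost correction to the safety section and the data collection is worth making.

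**What to change.** 1. State in the safety section that the exemption covers only non-serious events and only the reporting route. Every event that meets a seriousness criterion is then recorded and reported, whether or not it was expected.
2. Prespecify a short list of knee- and treatment-related events. Record it identically in both arms at the existing 3, 6, 12, 18 and 24-month adverse event collections, regardless of expectedness, and base the between-arm comparison on that list.
3. Present expected recovery events separately from the others, so that ordinary post-operative symptoms do not dominate the MAT count.

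The cost is a sentence or two in the safety section, a few added form items at visits that already collect adverse events, modest extra data entry, and a higher reported event count. Events waived before the change may not be recoverable, so the results should say from when the common list was in use.
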